## Abstract

**Background:**

Family carers play a crucial role in supporting the health and well-being of people with intellectual disabilities. Given their role and responsibilities, many family carers experience significant and ongoing stress and mental health difficulties. Programmes and interventions which provide training and support to family carers have been shown to have a positive impact on levels of stress and quality of life. However, these are often face to face which can create barriers to full participation. Online interventions have been shown to offer flexibility in delivery compared with traditional face-to-face approaches. The primary objective of this study is to determine the feasibility of delivering the Carers-ID online intervention, while the secondary outcome is improved mental health in family carers of people with intellectual disabilities.

**Methods:**

Family carers (*n* = 120) will be randomised to receive the intervention (*n* = 60) or assigned to a wait-list control (*n* = 60) group. The intervention (www.Carers-ID.com) consists of 14 modules which cover topics including the following: promoting resilience, providing peer support, reducing anxiety, managing stress, accessing local supports and managing family conflict and information for siblings who are carers. The intervention has been co-produced with voluntary sector organisations and family carers and tested for acceptability. Primary outcomes for this study include acceptability and feasibility of the outcome measures, recruitment, participation and retention rates and effect sizes. Secondary outcomes will be completed at three time points (baseline, following intervention completion and 3 months after completion). These include the following: the Depression, Anxiety and Stress Scale, the Warwick–Edinburgh Mental Well-being Scale, the Resilience Scale and the Social Connectedness Scale Revised. Participants (*n* = 12) who have taken part in the intervention arm of the research will be invited to participate in semi-structured interviews as part of the process evaluation.

**Discussion:**

The Carers-ID intervention provides an online resource for family carers to support their mental health and well-being and promote their resilience. It represents an affordable and accessible means of delivering such support. Testing the feasibility of the intervention and related trial procedures is required to determine whether a full-scale randomised controlled trial to evaluate the intervention’s effectiveness is warranted.

**Trial registration:**

ClinicalTrials.gov: NCT05737823

## Background

The majority of people with intellectual disabilities are living at home with their family, and family carers are providing ongoing and multifaceted care for their family members across the lifespan. Care can include any or all of the following: medication management, monitoring a physical condition, direct care, arranging and managing community presence and participation, liaising with professionals, supportive interventions, and behaviour management [1]. As approximately 77% of people with ID in England lived with their families in 2017–2018 [2], family carers play a crucial role in supporting their health and well-being. However, many family carers experience significant and ongoing stress and mental health difficulties [3, 4]; many also experience the positive aspects of caring for a family member who has ID [5, 6].

Programmes and interventions which provide training and support for family carers have been shown to have a positive impact on the following: levels of stress and feelings of confidence [7], child socialisation [8], and quality of life [9]. However, some family carers may face barriers in taking part in such interventions including time, family pressures, cost, and availability of services [10]. Online programmes offer greater flexibility of delivery and have been shown to offer comparable outcomes to more traditional treatment approaches in areas such as parenting styles [11], knowledge, and self-efficacy [12]. However, while online programmes show tangible benefits for family carers, few have been designed in collaboration with carers to better address their needs (Forbes T, Brown M, Marsh L, Truesdale M, McCann E, Todd S, et al: Online support programmes for family carers of people with intellectual disabilities: systematic review of the international evidence base, under review).

The COVID-19 pandemic made access to face-to-face care and support even more challenging for families, with some services offering online alternatives [13, 14]. While this created challenges for many, including access to reliable technology, it has also provided opportunities, such as reduced travel and delivery costs, and improved access to programmes [15].

A previous study conducted in 2021 by the same authors explored the impact of the COVID-19 pandemic on family carers. Based on these findings, a programme to support family carers of people with Profound and Multiple Intellectual Disabilities was developed — www.Carers-ID.com. The programme, co-produced with family carers and voluntary sector organisations across the UK and Ireland, sought to provide connectedness, reliable and easily accessible evidence-based materials and information on how to support mental health.

### Aim and objectives

The current study will be conducted in line with the updated Medical Research Council (MRC) framework for the development of complex interventions [16]. According to the framework, testing of intervention procedures, establishing recruitment and retention rates and determining a suitable sample size are key elements in the development of complex interventions. Therefore, the primary aim of this study is to determine the feasibility of conducting a large-scale effectiveness trial of the Carers-ID intervention. Specifically, we will determine the following:Recruitment, retention and attrition rates of participation in the trial.Intervention engagement and adherencePotential effect sizes and variability to inform a sample size calculation in an effectiveness trialFeasibility of collecting outcome data using measures of stress, anxiety, depression, resilience and well-being in assessing the impact of the intervention on family carers

The secondary aims are as follows:Examine impact on family carers mental health outcomes (stress, anxiety, depression, well-being and resilience) to guide a future trial.

## Methods

### Design

This is a randomised controlled feasibility design utilising a wait-list control with data collection at baseline (T0), on intervention completion, 2 weeks after baseline (T1) and at 3 months from baseline (T2). It will employ a qualitative process evaluation to explore acceptability of the outcome measures [17]. This trial is registered with the US National Library of Medicine, Clinical Trials Register (ID: NCT05737823), and will be reported in accordance with the Consolidated Standards of Reporting Trials (CONSORT) statement for pilot and feasibility studies [18]. Table 1 describes the flow of participants through the trial and the schedule of intervention and assessment.

**Table 1 Tab1:** Schedule of intervention and assessment

	Intervention group	Control group
**Time 1 — baseline (T0)**	Baseline measures	Baseline measures
**2 weeks**	Complete intervention	No active treatment
**Time 2 — 2 weeks after baseline (T1)**	2nd measures	2nd measures
**Interviews**	Acceptability interviews	No interview completed
**Time 3 — 3 months from baseline (T2)**	3rd measures	3rd measures
**Access to intervention**	-	Gain access to intervention

### Participants and recruitment

Based on previous studies [19, 20] and best practice guidelines [19, 21] we estimate, we will need to recruit between 100 and 120 family carers who will be randomised to receive the intervention (*n* = 60) or assigned to a wait-list control (*n* = 60) group. The sample characteristics will be similar to the target population of the future large-scale effectiveness trial. Participants will be UK adults > 18 years of age and will be caring for a family member with an ID (people with all levels of ID). As this is a feasibility trial, the sample size is not intended to detect a statistically significant difference. However, these numbers will be sufficient to allow us to test the trial methodology and acceptability and feasibility of our psychometric measures [22, 23]. Data gained from this study will allow us to calculate a sample size for a future effectiveness trial.

Participants will be recruited through our voluntary sector partners. Letters of invitation and information sheets will be sent out to members of our partner organisations to inform them of the study trial. Those interested in taking part will contact the research team if they require further information or to indicate their wish to participate.

For the process evaluation, participants (*n* = 12) who have taken part in the intervention arm of the study will be invited to participate in an online interview. An invitation letter and information sheet will be sent to all participants in the intervention group by the researcher. Those interested in taking part will contact the research team if they require further information or to indicate their wish to participate.

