## Discussion

Interventions for family carers with a training and support component have been shown to be effective in reducing levels of stress and improving quality of life [7–9]. However, these interventions are often delivered face to face, which can be a barrier to some family carers’ participation [10]. The online delivery of the current intervention offers flexibility, removing these barriers [11, 12] and encouraging and promoting participation. Despite the potential benefits of the Carers-ID intervention, its feasibility is unknown.

The Carers-ID intervention was co-designed with family carers of people with ID and voluntary sector partners and is therefore directly relevant to their lives. Our initial testing has shown that the programme is acceptable to family carers who felt that providing peer support and the opportunity to talk to other carers was an important element of the work. However, our use of convenience sampling in the absence of a sampling frame from which to draw a list of eligible participants may mean that our sample lacks representativeness to the wider population of family carers of people with ID. We intend to address this issue by recruiting from across the four countries of the UK and providing all who are interested in taking part with the opportunity to do so.

The mixed-methods design in the current study will provide important information on the feasibility of the Carers-ID online intervention. It will provide us with useful data on how our chosen outcome measures perform while also contributing information on the mental health of family carers. Findings from this trial will inform the appropriateness of progression to a phase III effectiveness trial, in addition to offering further recommendations to the content of the intervention, if required.

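### The stated entry rule admits carers who helped build, tested or already used Carers-ID, and no named item records earlier use or control-arm use before T2

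*Protocol article*

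**What the plan says.** Five parts of the protocol article bear on this.

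- **Who built and tried the programme.** The Discussion says "The Carers-ID intervention was co-designed with family carers of people with ID and voluntary sector partners". The Abstract (Methods) adds: "The intervention has been co-produced with voluntary sector organisations and family carers and tested for acceptability". The Discussion reports a result from that work: "Our initial testing has shown that the programme is acceptable to family carers". Some family carers have therefore already seen the programme.
- **How carers are found.** Participants and recruitment says "Participants will be recruited through our voluntary sector partners" and "Letters of invitation and information sheets will be sent out to members of our partner organisations". It names no other route.
- **Who may enter.** The same section says "Participants will be UK adults > 18 years of age and will be caring for a family member with an ID". The Discussion speaks of "providing all who are interested in taking part with the opportunity to do so". No exclusion for earlier involvement or use is stated.
- **What controls receive.** Table 1 in Design shows the control arm's two-week period as "No active treatment", with access given after the T2 measures.
- **What is recorded.** Secondary outcomes measures gives demographics such as age, sex, country and relationship. Primary outcomes gives activity within the online intervention (time spent, modules accessed), to judge engagement and adherence. Neither names earlier use, or control-arm use before T2.

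**The concern.** A wait-list comparison relies on controls not having had the intervention until their last measurement. Under the entry rule as written, a carer who advised on the modules or took part in the acceptability testing can be randomised. In the control arm that carer counts as untreated. In the intervention arm that carer is not a new user.

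Two of the trial's products could be affected:

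- **Effect size.** Effect sizes and variability are listed among the primary outcomes and may inform the next trial's sample size. Earlier exposure that leaves less to gain would pull the contrast towards zero.
- **Feasibility results.** Progression rests on more than 80% for completion of measures and for participation and retention, and interviews with 12 intervention-arm carers assess acceptability. Carers with a stake in the programme may stay longer, use it more and judge it more kindly. Randomisation does not correct this, because these rates are not between-arm contrasts.

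Controls opening the site during follow-up is a separate mechanism from earlier exposure. It threatens the same contrast and is likewise not recorded in any named item.

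**Working it through.** **The plan's own figure.** The target is 100 to 120 carers, and 60 + 60 = 120 is the top of that range. The article gives no alpha, power, effect size or SD, so there is no power calculation to reproduce.

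**Attenuation of the contrast.** Inputs that are not in the article and are assumed here:

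- A share p of each arm is already exposed. Randomisation makes the shares equal in expectation.
- Exposed carers gain a fraction g of the full benefit.
- The SD is unchanged at 1.
- The true standardised difference d is 0.4, for illustration.

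The observed difference is d × [(1 − p) + p × g]. With g = 1 it equals d, so nothing is lost. With g = 0, the worst case in this model, it is d(1 − p), and a sample size based on it grows by 1/(1 − p)². For the future trial, n per arm = 2(1.96 + 0.84)²/d², at two-sided 0.05 and 80% power.

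| p | exposed of 120 | observed d (g = 0) | inflation | n per arm |
|---|---|---|---|---|
| 0% | 0 | 0.40 | 1.00 | 99 |
| 5% | 6 | 0.38 | 1.11 | 109 |
| 10% | 12 | 0.36 | 1.23 | 122 |
| 20% | 24 | 0.32 | 1.56 | 154 |
| 30% | 36 | 0.28 | 2.04 | 201 |

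**Compared with sampling error.** The 95% half-width for d is about 1.96 × √(2/60) = 0.36 with 60 per arm, and 1.96 × √(2/48) = 0.40 with 48 per arm (80% retained). For p of 5% to 20% the shift is 0.02 to 0.08, well inside that. The shift is systematic, however, so a larger sample would not remove it.

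**Retention criterion.** Overall retention = (1 − p) × rate in new users + p × rate in exposed carers. Assume 78% in new users and 100% in exposed carers:

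- p = 5%: 0.95 × 78% + 5% = 79.1%, still a miss.
- p = 10%: 0.90 × 78% + 10% = 80.2%, now a pass.

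This matters only if the true rate lies close to the threshold.

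**Interviews.** Two or three earlier contributors among 12 interviewees would be 2/12 = 17% or 3/12 = 25% of the acceptability evidence.

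**The case against.** The strongest reply is that this is a condensed article. It gives one sentence of inclusion criteria and no exclusion list at all, and the full protocol, which is not shown, may hold more. The demographics are introduced with *such as*, so they are not a complete baseline form. The sentence offering a place to everyone interested answers the convenience-sampling limitation; it was not written as an eligibility rule. These points lower the certainty. They do not remove the point, because the entry rule that is stated, applied as it stands, lets exposed carers in.

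A reader might infer more than the article supports:

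- *That recruitment runs only through the organisations that built Carers-ID.* No other route is named and the label is shared, but the article does not say that the two sets are identical. According to the Background, co-production covered the UK and Ireland and the programme was for carers of people with profound and multiple ID; the trial takes UK carers for all levels of ID. Members of an organisation are also not necessarily the individuals who designed or tested the site.
- *That exposure does carry into both arms and does dilute the contrast.* No number of exposed carers is given, and nothing says that any will enrol.
- *That the site was already in public use.* Its address is printed, but the article does not say whether access was open. Giving controls access after T2 and logging module use would both fit controlled access.

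It is also fair that the trial is not sized to test the contrast, that effect sizes only *may* inform the next trial alongside previous studies, and that attenuation would make that trial larger, not underpowered.

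**Conclusion.** The point holds as a risk of unknown size, and the remedy is a cheap improvement. The stated eligibility admits carers who helped build, tested or used Carers-ID, and no named item would show how many there were or whether controls used the site before T2.

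Under the model above, the effect on the contrast runs from none (exposed carers still benefit fully) to a factor of 1 − p (they gain nothing further). The inflation factors of 1.23 to 2.04 need an assumed 10% to 30% exposure with no further benefit, so they are illustrations and not expected values. Earlier exposure is spread over both arms in expectation, so it attenuates the difference and does not favour either arm. Flattering of retention, engagement and acceptability is plausible, but the article has no data on how earlier contributors behave.

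It would go too far to say that the trial could not speak to carers new to the programme. Even at p = 30%, 120 − 36 = 84 of 120 would be new. Without a record, though, those 84 could not be separated from the rest, and that is difficult to repair afterwards.

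**What to change.** 1. In Participants and recruitment, add one screening question on whether the carer took part in designing or testing Carers-ID or has already used it, and exclude those who answer yes.
2. If exclusion is unwelcome to the partner organisations, record the answer at baseline and report the feasibility rates and effect sizes with and without these carers. Also state how many of the 12 interviewees were earlier contributors.
3. Add one item to the control arm's T1 and T2 questionnaires asking whether the carer has opened Carers-ID since joining. Report the percentage as a feasibility result, since it helps show whether an individually randomised wait-list is workable in the next trial.

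The target of 120 is unchanged. The cost is one eligibility line, one screening question, one extra questionnaire item and, with exclusion, the loss of a few otherwise eligible carers.

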### The intervention

The intervention (www.Carers-ID.com) is delivered online and comprises video and audio accounts of family carers’ experiences, peer-to-peer support, resources and activities which promote resilience and improve mental health. Carers-ID consists of 14 modules which cover topics including the following: promoting resilience, providing peer support, reducing anxiety, managing stress, accessing local supports and managing family conflict and information for siblings who are carers. It also shares examples of carers’ experiences of the COVID-19 pandemic and offers day-to-day accounts of successful strategies individuals used to improve their mental health. Our research showed that family carers wanted to feel connected to others and enjoyed sharing their experiences, and the Carers-ID intervention connects family carers with each other so they can provide peer support.

### Outcomes and success criteria

#### Primary outcomes

Criteria to assess the feasibility of progressing to a large-scale effectiveness trial include the following:Acceptability and feasibility of the outcome measures (completed by > 80% of family carers)Sufficient recruitment (> 90 carers) and participation and retention rates (> 80% of family carers)Effect sizes and estimate of variability (standard deviation), along with data from previous studies, may inform a sample size for a future effectiveness trial.

The primary outcome of this trial is to determine the feasibility of conducting a future effectiveness trial of the Carers-ID intervention, including acceptability and feasibility of the outcome measures, recruitment, participation and retention rates and effect sizes and estimates of variability.

Data on numbers of participants identified, recruited, commenced and finished in the intervention will be collected throughout the study. Reasons for declining participation and reasons for drop out will be recorded where possible. Feasibility of using the stress, anxiety, depression, resilience and well-being outcomes will be assessed through number of participants completing pre, post and follow-up measures. Acceptability of measures will be assessed qualitatively through semi-structured interviews (see below). We will also collect data on participant’s activity within the online intervention, including total time spent on the intervention and number of modules accessed, to enable us to assess intervention engagement and adherence.

#### Secondary outcomes measures

Our psychometrically validated outcome measures comprise the Depression, Anxiety and Stress Scale-21 [24], the Warwick–Edinburgh Mental Well-being Scale [25], the Resilience Scale [26] and the Social Connectedness Scale Revised [27]. Participant demographics such as age, sex, country (England, Scotland, Wales and Northern Ireland) and relationship to person with ID will also be collected.

The Depression, Anxiety and Stress Scale-21 items (DASS-21) [24] are a set of three self-report sub-scales designed to measure the emotional states of depression, anxiety and stress. Each of the three DASS-21 sub-scales contains 7 items, with 21 items in total. Items are rated on a 4-point Likert scale, from ‘Did not apply to me at all’ to ‘Applied to me very much or most of the time’. Scores for depression, anxiety and stress are calculated by summing the scores for the relevant items and multiplying by 2, with potential scores ranging from 0 to a maximum of 42, as scoring is based on the full 42-item version [24]. The scale has excellent reliability, with Cronbach’s alphas of 0.94, 0.88 and 0.93 for depression anxiety and stress respectively [24].

The Warwick-Edinburgh Mental Well-being Scale (WEMWBS) was developed to enable the measurement of mental well-being and has excellent reliability with a Cronbach’s alpha of 0.91 [25]. The WEMWBS is a 14-item scale of positively worded statements covering feeling and functioning aspects of mental well-being. The 14 statements have five response categories from ‘none of the time’ to ‘all of the time’. The WEMWBS is scored by summing the scores for each of the 14 items, which are scored from 1 to 5. Scores range from 14 to 70 with higher scores indicate greater positive mental well-being [25]. Previous research found that a change of about 3 or more points can be considered clinically significant [26].

The 25-item Resilience Scale was developed as a general measure of resilience for adults across the lifespan [26]. Participants respond by either agreeing or disagreeing with statements on a scale of 1 (disagree) to 7 (agree). The responses are summed (minimum score of 25 to a maximum of 175) with higher score reflecting stronger resilience. Reported Cronbach’s alpha for this scale range from 0.87 to 0.95 [27].

The 20-item Social Connectedness Scale Revised (SCS-R) is used to assess the extent to which persons feel connected to others in their surrounding social area [28]. Responses are on a Likert scale with 1 ‘strongly disagree’ to 6 ‘strongly agree’. Negatively worded items are reverse scored and summed together with the positively worded items to create a score ranging from 20 to 120. Higher scores on the SCS-R reflect a stronger sense of social connectedness. The scale has a Cronbach’s alpha of 0.92 [28].

